## Abstract

**Background:**

Breathlessness in advanced disease causes significant distress to patients and carers and presents management challenges to health care professionals. The Breathlessness Intervention Service (BIS) seeks to improve the care of breathless patients with advanced disease (regardless of cause) through the use of evidence-based practice and working with other healthcare providers. BIS delivers a complex intervention (of non-pharmacological and pharmacological treatments) via a multi-professional team. BIS is being continuously developed and its impact evaluated using the MRC's framework for complex interventions (PreClinical, Phase I and Phase II completed). This paper presents the protocol for Phase III.

**Methods/Design:**

Phase III comprises a pragmatic, fast-track, single-blind randomised controlled trial of BIS versus standard care. Due to differing disease trajectories, the service uses two broad service models: one for patients with malignant disease (intervention delivered over two weeks) and one for patients with non-malignant disease (intervention delivered over four weeks). The Phase III trial therefore consists of two sub-protocols: one for patients with malignant conditions (four week protocol) and one for patients with non-malignant conditions (eight week protocol). Mixed method interviews are conducted with patients and their lay carers at three to five measurement points depending on randomisation and sub-protocol. Qualitative interviews are conducted with referring and non-referring health care professionals (malignant disease protocol only). The primary outcome measure is 'patient distress due to breathlessness' measured on a numerical rating scale (0-10). The trial includes economic evaluation. Analysis will be on an intention to treat basis.

**Discussion:**

This is the first evaluation of a breathlessness intervention for advanced disease to have followed the MRC framework and one of the first palliative care trials to use fast track methodology and single-blinding. The results will provide evidence of the clinical and cost-effectiveness of the service, informing its longer term development and implementation of the model in other centres nationally and internationally. It adds to methodological developments in palliative care research where complex interventions are common but evidence sparse.

**Trial Registration:**

ClinicalTrials.gov: NCT00678405

ISRCTN: ISRCTN04119516

## Background

Intractable breathlessness can completely dominate a patient's life causing physical disability, loss of independence and dignity and lowered self-esteem [1-3]. It is common in advanced disease, both malignant and non-malignant. In chronic obstructive pulmonary disease (COPD) and heart failure it is nearly universal by the time of death, its prevalence reaching over 50% in both conditions in the advanced stages. It occurs in 49% of the general population with all cancers [4], and in 90% of those with lung cancer [5]; these figures will rise as deaths from mesothelioma peak in 2016 [6]. The incidence of breathlessness in cancer is second only to that of pain [7]. Breathlessness is also a devastating accompaniment in less common cardio-respiratory diseases, e.g. interstitial lung disease and cystic fibrosis. Despite its prevalence breathlessness remains a poorly controlled symptom in which traditional pharmacological interventions are frequently ineffective [1,8,9].

However, patterns of breathlessness in cancer and COPD differ. Once patients with cancer become breathless they usually have a very short time to live and may become breathless at rest, whereas patients with COPD may live with gradually worsening symptoms and increasingly devastating consequences for years. As a result, patients with different diagnoses and their carers may have different needs [10]. The effects on the patient and family with malignant or non-malignant disease include increased social isolation, reduced activity, chronic anxiety, loss of employment and other changes in roles and perceived status [3,11]. Further, the economic burden to the healthcare system is significant [12].

Advances in the palliation of breathlessness include non-pharmacological intervention services to reduce or contain the severity of the sensation and, for patients with COPD, pulmonary rehabilitation programmes [13,14]. Non pharmacological methods for the management of breathlessness acknowledge the cognitive and emotional component [9]. Breathlessness services developed for patients with lung cancer have been formally evaluated with positive outcomes in terms of distress due to breathlessness, functioning and quality of life [15-17] however each of these studies had limitations: all were clinic based (patients were not seen at home); two were randomised controlled trials but one lacked published power calculations; and the outcomes reported by all were limited to patient outcomes i.e. none reported staff satisfaction, the views of referrers, or carer outcomes. Breathlessness studies have identified significant suffering among carers who report severe anxiety and helplessness as they witness their partners' suffering and feel powerless to reduce it [3].

In November 2003, a pilot Breathlessness Intervention Service (BIS) was set up at Addenbrooke's Hospital consisting of a clinical specialist physiotherapist and palliative care consultant [18]. BIS aims to manage the symptom of breathlessness in patients with any disease (malignant or non-malignant), using a rehabilitative approach. It uses a 'toolkit' of interventions including: evidence-based non-pharmacological interventions (psychological, social and physical); palliative care input (e.g. end of life issues, psychosocial issues, family concerns); and pharmacological review. Thus BIS seeks to enhance the self-management of breathlessness. Uniquely, care is located flexibly in clinic or in patients' own homes, as appropriate. Referrals come from medical specialists, GPs and allied health professionals (with medical consent).

From the outset its development and evaluation was grounded in the MRC's framework for the development and evaluation of complex interventions [19]. Following the developmental work conducted over the past twelve years (Pre-clinical-Phase II [3,10,18,20,21]), BIS is now undergoing evaluation in a Phase III definitive randomised controlled trial (RCT). This paper presents the Phase III RCT protocol.

The aim of Phase III is to address the following research questions:

1. Is BIS more effective than standard care for patients with intractable breathlessness from advanced malignant or non-malignant disease?

2. Does it reduce patient and carer distress due to breathlessness, and increase patients' sense of mastery of the symptom?

3. What are the experiences and views of those who use BIS, their informal carers and the clinicians who refer to it?

4. Is BIS cost-effective?

## Methods/Design

### Design

Phase III is a mixed method pragmatic fast track single blinded randomised controlled trial of BIS versus standard care.

BIS offers care and support to patients with malignant or non-malignant conditions. Due to the differing disease trajectories of these two groups, BIS uses two broad service models: one for patients with malignancies (intervention over a two week period) and one for patients with non-malignant conditions (intervention over a four week period), summarised in Table 1. The trial therefore consists of two sub-protocols: one for patients with malignancies (four week protocol) and one for patients with non-malignant conditions (eight week protocol) (Figures 1 and 2).

**Figure 1 F1:**
[figure not shown]
**BIS Phase III measurement point flow chart for non-malignant conditions**. shaded area = intervention

**Figure 2 F2:**
[figure not shown]
**BIS Phase III measurement point flow chart - malignant conditions**. shaded area = intervention

**Table 1 T1:** Service model for the Breathlessness Intervention Service (BIS) at Addenbrooke's Hospital, Cambridge University Hospitals NHS Foundation Trust (March 2008)

Disease group course:	Non-malignant (nm) course	Malignant (m) course
Examples:	e.g. COPD, heart failure, neurological disorders	e.g. all cancers, UIP

Referral:	Post, fax, electronic	Post, fax, electronic

Assessment lead:	Clinical Specialist Physiotherapist or Clinical Specialist Occupational Therapist	Medical Consultant (i.e. sees a doctor earlier in the intervention than non-malignant patients)

BIS team:	Clinical Specialist Occupational Therapist Clinical Specialist Physiotherapist Medical Consultant	Medical Consultant Clinical Specialist Occupational Therapist Clinical Specialist Physiotherapist

Medical assessment:	May be required	Always required (review of pharmacological management at 1^st ^visit)

First appointment:	Maximum wait of 3 weeks for first appointment	Maximum wait of 1 week for first appointment

Range of face-to-face visits:	2-3	1 (with primary care professional)

Average no. of telephone contacts (with patient/primary care staff):	3	2

Ratio of face-to-face to telephone:	1:1	2:1

Average length of service contact:	4 weeks + 16 week follow up (from 1^st ^assessment) post any pulmonary rehab/other referral	2 weeks + 6 week follow up (from 1^st ^assessment) post any pulmonary rehab/other referral

Service outcome measures collected at first assessment:	• modified BORG at rest, self-reported, on exertion and on completion of exercise test • anxiety due to breathlessness at rest, self reported, on exertion and on completion of exercise test • physiological measures e.g. oxygen saturation, heart rate	• modified BORG at rest, self-reported, on exertion and on completion of exercise test • anxiety due to breathlessness at rest, self reported, on exertion and on completion of exercise test (if acceptable) • physiological measures e.g. oxygen saturation, heart rate

Non-pharmacological interventions:	1^st ^stage of intervention	More likely to be concurrent with pharmacological interventions

Pharmacological interventions:	2^nd ^stage of intervention	More likely to be concurrent with non-pharmacological interventions

1^st ^stage interventions (selection & application as clinically indicated):	The majority of these interventions are used with this group, & taught over a longer period of time: → explanation & reassurance → anxiety management → psychological support → hand-held fan → information fact sheets → emergency plan → positioning to reduce work of breathing (rest, recovery & activity) → breathing control → education to patient, carer & health care generalists → pacing & lifestyle adjustment → individualised exercise plan → relaxation & visualisation → airway clearance techniques → advice regarding nutrition & hydration → support to family & patient to utilise education & self-support programmes → sleep hygiene → smoking cessation prompt → brief cognitive therapy → pharmacological review → well-being intervention → hypnosis → mindfulness CD → referral to specialist services (see below)	More selective use & application of these interventions, & taught over a shorter period of time: → explanation & reassurance → anxiety management → psychological support → hand-held fan → information fact sheets → emergency plan → positioning to reduce work of breathing (rest, recovery & activity) → breathing control → education to patient, carer & health care generalists → pacing & lifestyle adjustment → individualised exercise plan → relaxation & visualisation → airway clearance techniques → advice regarding nutrition & hydration → support to family & patient to utilise education & self-support programmes → sleep hygiene → brief cognitive therapy → pharmacological review → well-being intervention → hypnosis → mindfulness CD → referral to specialist services (see below)

2^nd ^stage interventions:	Choice of 2^nd ^stage interventions dependent on outcome of first stage interventions: → further pharmacological review e.g. low dose opioids, anti-depressants, anxiolytics → referral to specialist services (see below) → referral for LTOT or SBOT assessment	2^nd ^stage interventions likely to be applied concurrently with 1^st ^stage interventions: →further pharmacological review e.g. low dose opioids, anti-depressants, anxiolytics →referral to specialist services (see below) →referral for LTOT or SBOT assessment

Other symptom management:	May be required	Frequently required

Documentation:	→ individualised patient plan → summary to patient of outpatient consultation with medical consultant → discharge summary to referrer with copies to GP, specialist services the patient was already in contact with (e.g. respiratory physicians), other involved health care professionals (e.g. district nurses, nursing home care staff)	→ individualised patient plan → summary to patient of outpatient consultation with medical consultant →discharge summary to referrer with copies to GP, specialist services the patient was already in contact with (e.g. respiratory physicians), other involved health care professionals (e.g. district nurses, nursing home care staff) → supplementary medical letters more common

Referrals:	→ Pulmonary rehabilitation → Specialist dietetic → Specialist psychological services → Hospice day services → other specialist assessment → Cardiac rehabilitation → other rehab services (n.b. these services usually have a wait time)	→ Palliative care specialist service (n.b. rapid access available) → Specialist psychological services → Hospice day services → other specialist assessment

While understanding that it is not possible or desirable to standardize all aspects of the Breathlessness Intervention Service (BIS) for individual patients, we have established a service model with a minimum set of core interventions. The norm is for consultations to occur in the patient's own home (with clinically reasoned variance)

LTOT = long term oxygen therapy

SBOT = short burst oxygen therapy

Based on methods piloted at Phase II [20,21], consented patients are randomised either to a 'fast-track' group where they receive BIS immediately or to a waiting list group (control condition) where they receive the intervention after a defined period on a waiting list during which time they receive standard care. The advantage of a fast-track design is that it has the strength of a RCT, but with greater acceptability as all patients receive the intervention. Due to the palliative status of the patients referred to BIS, and the existence of BIS prior to this proposed RCT, a traditional intervention and control group design (where the control group would be denied access to the service) would be unethical and unacceptable [22]. This alternative fast-track design proved highly acceptable at Phase II [20].

### Setting

BIS is a secondary care service which provides care in a community setting, predominantly seeing patients in their own homes. It principally takes referrals from the Addenbrooke's catchment area seeing patients from Cambridgeshire, Hertfordshire and Essex and, where practical, further afield.

### Intervention

Table 1 outlines the minimum core interventions delivered by BIS. The service provides a thorough psychological and physical assessment taking into account patient and carer needs and breathlessness triggers. A treatment plan is agreed and implemented incorporating a range of evidence-based non-pharmacological and pharmacological techniques relevant to the patient and their lifestyle, helping them to self-manage their symptoms. A personal emergency plan is agreed and practised, with each patient receiving a copy. Paper copies of quality controlled information leaflets are provided (also accessible via the internet).

### Standard care

For the purposes of this trial, 'standard care' is defined as specialist outpatient appointments in secondary care (e.g. respiratory, cardiology, neurology or oncology) which may include specialist nurse input, and primary care services.

### Sample

The clinical team screen all referrals to the service against the study inclusion and exclusion criteria (Table 2) and a screening log is maintained.

**Table 2 T2:** Inclusion and exclusion criteria

Inclusion criteria	Exclusion criteria:
Patients:	Patients/Carers:
(i) appropriate referral to BIS	(i) unable to give informed consent;
(ii) aged 18 years+	(ii) previously used BIS;
(iii) any patient not meeting any exclusion criteria	(iii) demented/confused;
	(iv) learning difficulties;
	(vi) other vulnerable groups e.g. head injury, severe trauma, mental illness;
	(vii) not meeting all inclusion criteria.
Carer:	
(i) informal carers (significant others, relatives, friends or neighbours) of Phase III RCT recruits	
(ii) aged 18 years+	
(iii) any carer not meeting any exclusion criteria.	

### Recruitment

A Patient Information Sheet is sent by first class post to eligible patients inviting participation in the trial. On the sub-protocol for patients with non-malignant conditions a second mailing is sent if there is no response within a week. On the sub-protocol for patients with malignancies a BIS clinician conducts a telephone follow-up if there is no response within a week; this clarifies that the patient has received a recruitment pack and establishes whether or not they would like to participate in the trial. If the patient (from either sub-protocol) refuses trial participation, or there is still no response, the service arranges to see the patient in the usual way and they are not recruited to the trial. If the patient responds positively to a recruitment letter a researcher contacts them to arrange to visit and explain the study in more detail, answer any questions, obtain informed consent, conduct the baseline interview (t1) and identify their lay carer.

If their lay carer is present at the patient's t1 then they are directly invited to participate in the study. If they are willing then the researcher answers any questions, obtains informed consent and conducts the carer baseline interview (t1). Where possible, carers are interviewed separately from patients as this was found to be important in the Phase I of the evaluation [3]. If the lay carer is not present then a recruitment pack (similar to that for the patient) is either left for them with the patient, or posted to them, depending on circumstances. They are then approached in the same way as for patients.

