### Randomisation

Randomisation is carried out within 24 hours of the baseline interview (t1) by a third party (Addenbrooke's clinical trials' team) sequentially opening sealed opaque envelopes containing the random group allocation previously generated using a computer programme by the study statistician (University of Cambridge). The envelopes were set up by an administrator at University of Cambridge. Patients are allocated to the fast track group or waiting list group with an equal 1:1 allocation ratio using the method of stratified randomisation, with disease group (malignant, non-malignant) as the single stratifier.

Patients are informed of the outcome of randomisation by the clinical trials' team, by telephone. BIS is then notified of the outcome of randomisation by the clinical trials' team (by secure email) in order that the service can book the first appointment with the patient in-line with the study protocols. The researcher is then notified that randomisation has occurred, and that the patient and service have been informed, but not the outcome of the randomisation. The purpose and need for single blinding is explained to patients and carers at the recruitment visit and they are reminded at the start of each subsequent blinded interview to try not to let the researcher know their group allocation. In addition, all data are handled using study identity numbers; group allocation identifiers will only be added at the analysis stage. A detailed description and discussion of single-blinding, piloted at Phase II, has been given elsewhere [20].

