### Measurement points

The data collection points (interviews) are outlined in Figures 1 and 2. Baseline interviews are collected for all respondents, regardless of diagnostic group, at t1, prior to randomisation.

For patients with non-malignant conditions and their carers, t2 occurs two weeks post t1 and the commencement of BIS (fast track group) or the entering of the waiting list (waiting list group), and t3 occurs four weeks post commencing BIS (fast track group) or the entering of the waiting list (waiting list group). The waiting list group have a t4 interview scheduled two weeks post their commencement of BIS (six weeks from t1). T5 occurs eight weeks after t1 (i.e. on discharge from BIS for the waiting list group or four weeks from discharge for fast track group). This model was successfully piloted at Phase II [20]. Therefore for those randomised to the fast track group, t2 and t3 represent mid-point and completion of the BIS intervention, for comparison with these same time-points in the contemporaneous control condition for those randomised to the waiting list group.

Due to the shorter time frame of the service model for patients with malignancies, there are no t2 or t4 interviews for patients or their carers in this group. Instead, t3 is conducted 2 weeks post t1 i.e. on discharge from BIS for the fast track group or just prior to commencement of BIS for the waiting list group. T5 then occurs four weeks after t1 (i.e. on discharge from BIS for the waiting list group or two weeks from discharge for fast track group). Therefore t3 is the time-point marking completion of the BIS intervention for those randomised to the fast track group, and the control condition in those randomised to the waiting list group.

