### Analysis

The same methods will be used to address the two research questions concerning the effectiveness of BIS and patient and carer distress and patient mastery of symptoms. Analyses will be presented separately for non-malignant and malignant participant groups. The baseline comparability of the arms will be examined by presenting pre-randomisation means and proportions of patient characteristics at timepoint t1 by randomised arm. The research questions will be addressed by cross-sectional comparison at t3 (end of intervention in fast track arm versus control condition in waiting list arm), using analysis of covariance adjusting for the baseline of the outcome within a linear regression framework. For the non-malignant group, this will be supported with the same analysis at t2.

Analyses will be primarily on an intention to treat basis. Secondary sensitivity analyses will be performed if there are deviations to the intervention protocol (requiring per protocol analysis) or there are baseline imbalances (requiring analysis adjustment). A graph will summarise the mean response over the time-points, with estimates and 95% confidence intervals for differences both between arms and within each arm over time from t3 to t5 (using paired t-tests). If a chi-squared test does not indicate that the t3 randomised effects are dissimilar in malignant and non-malignant groups, a simple average combined effect will be estimated with a narrower overall confidence interval to inform Phase IV. All analyses will be two-sided and assessed at the 5% significance level using SPSS software.

Qualitative data will be transcribed by an independent transcription company, checked and anonymised before analysis; transcripts will then be imported into NVivo software to facilitate the conduct of framework analysis [32]. Mixed method analyses will purposively sample qualitative data, based on quantitative findings.

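### Carers absent from the patient's t1 visit would normally give consent and baseline after allocation, yet that baseline is called pre-randomisation and is the covariate for carer outcomes

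*Protocol article*

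**What the plan says.** Four sections of the protocol article bear on this.

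- **Recruitment.** A carer who is present at the patient's t1 can be consented and interviewed there. For the others: "If the lay carer is not present then a recruitment pack (similar to that for the patient) is either left for them"; otherwise it goes by post. The next step is: "They are then approached in the same way as for patients". For patients with non-malignant disease that route means "a second mailing is sent if there is no response within a week"; for those with malignant disease, "a BIS clinician conducts a telephone follow-up if there is no response within a week". A positive reply leads to a researcher visit for consent and the baseline interview.
- **Randomisation.** "Randomisation is carried out within 24 hours of the baseline interview (t1) by a third party". The patient is the unit: "Patients are allocated to the fast track group or waiting list group with an equal 1:1 allocation ratio". The patient then hears the result by telephone, and the service is told so that it can book the first appointment.
- **Measurement points.** "Baseline interviews are collected for all respondents, regardless of diagnostic group, at t1, prior to randomisation". The schedule in this section covers patients and their carers.
- **Analysis.** Effectiveness and distress, including carer distress, are compared at t3 "using analysis of covariance adjusting for the baseline of the outcome".

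**The concern.** The steps for an absent carer take days or weeks, while the step from the patient's t1 to randomisation takes at most one day. Nothing in the article makes the second wait for the first. Followed as written, the plan therefore gives some carers a baseline taken when the household already knows its arm. In the fast-track arm it may also be taken after the service has begun.

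Two things are at stake for the carer outcomes.

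1. **The covariate may be affected by treatment.** If late fast-track carers have already improved when their baseline is recorded, adjusting for it removes part of the effect being estimated.
2. **Consent comes after allocation.** Carers may agree or decline differently by arm, and randomisation does not protect against that. In the malignant group the reminder call comes from a service clinician, and the service has been told the allocation.

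Carer distress is one of the three parts of research question 2, beside patient distress and patient mastery. The Background also notes that earlier evaluations reported no carer outcomes.

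**Working it through.** **1. The plan's own figure.** The Sample size section gives 26 patients per arm per disease group (2-point difference, SD 2.5, 80% power, two-sided 5% t-test). The normal approximation gives 2 × (1.96 + 0.84)² × 2.5² / 2² ≈ 24.5, so 25. The t-test calculation gives 25.5, so 26, with power 0.807. The figure reproduces. It concerns patients only; the article gives no sample size, SD or effect for carers.

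**2. Timeline, counting from the patient's t1 as day 0.**

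| Event | Day | Source |
|---|---|---|
| Pack left or posted for the absent carer | 0 or later | Recruitment |
| Randomisation, then the patient is told | by day 1 | Randomisation |
| First reminder if the carer has not replied | 7 or later | Recruitment |
| Carer consent and baseline in that branch | 7 or later | Recruitment |
| t3, malignant group | 14 | Measurement points |
| t2, non-malignant group | 14 | Measurement points |
| t3, non-malignant group | about 28 | Measurement points |

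In the no-response branch the carer's baseline falls at least 7 − 1 = 6 days after randomisation. In the malignant group at most 14 − 7 = 7 days then remain to t3. In the non-malignant group at most 7 days remain to t2 and about 28 − 7 = 21 to t3. A carer who replies promptly is seen sooner, but is in time only if seen before the envelope is opened.

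**3. Effect on the adjusted estimate.** The ANCOVA estimate is

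(mean outcome, fast track − waiting list) − β × (mean baseline, fast track − waiting list).

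If a share f of fast-track carers has a late baseline already lower by d points, the second bracket changes by −f × d. The estimated benefit then shrinks by about β × f × d.

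None of β, f and d is in the article. A simulation of 3,000 runs per setting used 26 per arm, SD 2.5 and a true effect of −2. All three are borrowed from the patient calculation, and n = 26 amounts to one analysed carer for every analysed patient. With equal SDs, β equals the baseline–outcome correlation. The ranges tried were β 0.3 to 0.7, f 25% to 50% and d 0.5 to 2 points. Selected results:

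| β | f | d | β × f × d | Simulated estimate | Power |
|---|---|---|---|---|---|
| 0.5 | 0 | – | 0 | −2.00 | 0.90 |
| 0.3 | 0.25 | 0.5 | 0.04 | −1.96 | 0.83 |
| 0.5 | 0.25 | 1 | 0.13 | −1.87 | 0.86 |
| 0.5 | 0.50 | 1 | 0.25 | −1.73 | 0.80 |
| 0.7 | 0.50 | 2 | 0.70 | −1.34 | 0.70 |

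Settings with no late carers returned −2.00 to −2.02, so simulation error is about 0.01 to 0.02. Across the grid the loss runs from 0.04 to 0.66 points. Power should be compared only within one value of β: without late carers it is 0.84 at β = 0.3, 0.90 at β = 0.5 and 0.98 at β = 0.7.

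**4. Direction.** If waiting-list baselines also move, what counts is the difference between the arms' shifts. The bias is towards the null when late fast-track baselines have improved relative to the waiting list, and away from it in the opposite case.

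**The case against.** The strongest reply is that the late timing is inferred. The Recruitment section labels the patient's and the carer's baseline alike as t1. The Randomisation section does not say whose t1 starts the 24 hours, and the Measurement points section states the rule outright. If randomisation follows the last t1 obtained, all three agree. The article also condenses a fuller protocol, which may set the order.

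This limits how firmly the point can be put, but does not remove it. The patient is the unit randomised, and the carer interview is named separately, so the patient's t1 is the natural reading. Waiting for a carer reached on day 7 or later would break the 24-hour rule for the patient's own interview. It would also leave a malignant-group patient 7 days or less between randomisation and a t3 fixed at two weeks from t1. These are steps the article states and that conflict; the problem is not a detail left out.

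Other objections stand. The patient primary outcome and its sample size are unaffected. The researcher who takes consent is not told the allocation, so any selection would come mainly from the carers or from the service's reminder call, and neither its size nor its direction is shown. The week's delay applies only to carers who do not reply at first.

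A reader might infer that late carers are usually interviewed after the service has started. The documents do not support that: prompt replies are possible, and Table 1 allows up to one week (malignant) or three weeks (non-malignant) before a first appointment.

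**Conclusion.** For carers absent from the patient's t1, the Recruitment, Randomisation and Measurement points sections cannot all be followed, unless the carer is reached within 24 hours or randomisation waits. The article states neither. Otherwise these carers' consent and baseline follow allocation, by at least 6 days in the no-response branch, and the planned ANCOVA adjusts for a value that allocation may have changed.

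The size cannot be derived. The range of 0.04 to 0.66 points rests on an assumed share late, baseline shift, slope, carer SD, carer effect of 2 points and number of carers. The top of the range needs half of the carers late and already 2 points better at baseline, which is the whole assumed effect. The bottom is negligible. A reader might take any one of these figures as the expected bias, or carry the concern over to the trial's main result. Neither is supported: the inputs are illustrative, and patient baselines precede randomisation.

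Severity is moderate and confined to secondary, carer outcomes.

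**What to change.** 1. **Reconcile the three sections.** State whether randomisation waits for an absent carer's baseline, and how the t1-based interview schedule then works. If it does not wait, state that such baselines may follow allocation and correct the sentence on all respondents.
2. **Record dates.** Hold each carer's consent and t1 dates against the patient's randomisation date.
3. **Fix the covariate rule.** Never use a value obtained after randomisation as the baseline covariate.
4. **Main carer ANCOVA.** Include the carers whose consent and t1 preceded randomisation. That status is settled before allocation, so the comparison between arms remains a randomised one.
5. **Sensitivity analysis.** Add late carers with baseline treated as missing and set to the overall pre-randomisation mean, or analyse without baseline adjustment. Either removes the covariate problem, but not selection at consent, which is why this is not the main analysis.

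Carers already enrolled can be handled by the same rule at analysis. A telephone baseline within the 24 hours is not proposed, because the Data collection interviews section specifies face-to-face interviews and the mode would change for absent carers only.

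The cost is some protocol wording and one date check. The main carer analysis loses some carers and precision, and applies to carers reached before randomisation, in practice mostly those present at the visit.
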